**Methods:**

In this multicenter randomized controlled trial, patients diagnosed in the Netherlands with stage 1A and 1B low-risk endometrial cancer, for whom adjuvant radiotherapy is not indicated (*n* = 282), are randomized. Patients allocated to the intervention group receive four follow-up visits during three years. Patients allocated to the control group receive 10–13 follow-up visits during five years, according to the Dutch guideline. Patients are asked to fill out a questionnaire at baseline and after 6, 12, 36, and 60 months. Primary outcomes include patient satisfaction with follow-up care and cost-effectiveness. Secondary outcomes include healthcare use, adherence to schedule, health-related quality of life, fear of recurrence, anxiety and depression, information provision, recurrence, and survival. Linear regression analyses will be used to assess differences in patient satisfaction with follow-up care between intervention and control group.

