Current evidence provides a multitude of reasons that support reduction of standard follow-up visits. First, there is no survival benefit in the detection of asymptomatic recurrences at routine follow-up, compared with symptomatic recurrence or interval detection [4, 5, 8, 16–18], probably because the recurrence rate of early-stage endometrial cancer survivors is low (3%) and because most recurrences (70%) present with symptoms [5]. The majority (70–100%) of the recurrences occur within three years [5]. Second, side-effects from treatments are found in only 6% of the stage 1 patients who received surgery (hysterectomy and salpingo-oophorectomy) alone [2, 19]. Third, follow-up visits evoke distress around the time of the visits [15, 17, 20–22]. Finally, alternative follow-up schedules in other cancer populations do not show decreased patient satisfaction or health-related quality of life (HRQoL) [23, 24]. At the same time, there are reasons to retain some follow-up care, including that follow-up is beneficial for patients for reassurance [15, 21, 25], to provide support for psychosocial, physical, and sexual problems [2, 3, 24], and to provide information [26] and tertiary prevention care [27].

These findings suggest that most early-stage endometrial cancer patients do not need intensive follow-up to detect recurrences, improve survival, or discuss consequences of treatment. However, patients may need *some* follow-up to detect information needs and provide psychosocial counseling. Therefore, a reduced follow-up schedule for low-risk, early-stage endometrial cancer patients should focus on eliminating unnecessary care, which is expected to result in decreased patient worry around visits, prevent wrong patient expectations, and save healthcare costs. At the same time, a minimal number of follow-up visits is needed to support necessary patient counseling and information provision [8–10].

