## Methods/Design

### Objectives and hypotheses

The aim of this study is to compare a reduced follow-up schedule of four visits in three years among low-risk, early-stage endometrial cancer survivors, with the schedule according to the current Dutch guideline that includes 10–13 visits in five years. Primary outcomes include patient satisfaction with follow-up care and costs-effectiveness from the healthcare perspective. Secondary outcomes include healthcare use, adherence to the indicated follow-up protocols, reasons for non-adherence, HRQoL, worry including fear of recurrence, anxiety and depression, satisfaction with information provision, healthcare providers’ satisfaction with follow-up schedule, time till recurrence, and survival.

We hypothesize that endometrial cancer patients in the intervention arm of the study are not less satisfied with the follow-up care and do not report worse HRQoL, fear of recurrence, anxiety, depression, and information provision satisfaction. We furthermore hypothesize that healthcare use and associated costs will be lower in the intervention arm, resulting in a cost-effective intervention. More precisely, we expect that by reducing the follow-up schedule from 10–13 to four visits, the costs of these visits will be saved, although some substitution might occur to care by the specialist, specialized nurse, or general practitioner. From a healthcare perspective, we expect this alternative follow-up schedule will save costs.

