### Sample size

The power calculation is performed on the first primary outcome “satisfaction with follow-up care.” The maximal difference between the groups that we find acceptable (non-inferiority margin) is 6 points (< 0.5 SD) on a scale from 0 to 100, with a standard deviation (SD) of 14.3 by [35], based on the rule of thumb as supposed for the EORTC_QLQ-C30 questionnaire [43]. Therefore, with alpha 0.05 and beta 0.80 we need a sample size of 180 (90 per study arm). In this sample size we assume that 30–50 centers will participate and as a consequence we adjusted the number needed in the analysis to account for the clustering of patients within hospitals. With an expected loss to follow-up of 20% and patient who die (16%) over five-year follow-up we need to include 282 patients. Assuming that 60% of the patients will participate, we need 470 eligible patients. In the Netherlands, 450 patients per year meet the inclusion criteria. Since not all hospitals will start inclusion at the same time, we expect an inclusion period of 2.5 years.

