### Statistical analysis

Data will be analyzed after one, three, and five years of follow-up. All patients will be included in the analyses and all patients will be analyzed according to the arm to which they were assigned (intention-to-treat). In addition, per protocol analyses will be conducted including patients who received follow-up care as intended in the trial arms. Intention-to-treat and per-protocol analyses are both important in non-inferiority trials. Data will be analyzed using descriptive statistics, linear, and logistic regression analyses. Primary outcome is satisfaction with follow-up care over three-year follow-up. The primary outcome will be analyzed one-sided. Secondary outcomes will also be analyzed as non-inferiority using 0.5 SD as a non-inferiority margin, but will be tested two-sided.

Multilevel multivariate linear and logistic regression analyses will be conducted for continuous and dichotomous outcomes, respectively. Analyses will include relevant pre-defined covariates to improve the power. Differential effects by fear of recurrence will be evaluated by adding the interaction term (group*moderator) to the model. We will carry out repeated measures analyses using multilevel linear mixed models, which accounts for the intra-patient dependency of the repeated measures. Missing outcomes will be assumed missing at random (MAR). An advantage of multilevel linear mixed models is that all patients can be included in the analyses, regardless of whether they have been missing some follow-up measurements. All tests will be considered significant if *p* < 0.05. Clinically meaningful differences will be determined with Norman’s “rule of thumb,” whereby a difference of > 0.5 SD indicates a threshold of discriminant change in health status scores of a chronic illness [43]. If we have the baseline data of a patient, we will include this patient in the analysis.

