## Discussion

Although the current guidelines in the Netherlands describe five years of hospital-based follow-up for women after their treatment for endometrial cancer, hardly any scientific evidence exists to support this timely and expensive practice which involves increasing resources due to the growing number of cancer survivors. Therefore, a critical evaluation of follow-up care for endometrial cancer survivors is needed. The current landscape of evidence predominantly focuses on transitioning follow-up care to nurses or primary care physicians [45]. However, we hypothesize that reducing the frequency of follow-up care would result in a higher cost-effectiveness through retaining levels of satisfaction and outcomes, while decreasing the costs of follow-up care. Outcomes of our trial may therefore evoke a new framing of the issue of follow-up care, by shifting the focus from transitioning care to eliminating unnecessary care, without disregarding a minimal level of follow-up care that is needed to provide adequate information, psychosocial support, and tertiary prevention [15, 21, 25]. Although Survivorship Care Plans did not increase satisfaction with information and care in a previous trial [30, 31], we expect that Survivorship Care Plans support symptom monitoring, thereby limiting the need for additional follow-up visits to detect symptomatic recurrences.

Patients who do not agree to participate in the trial may have higher needs regarding follow-up care and, for instance, higher levels of psychological distress. If our non-participation study shows differences between participants and non-participants, the results of the study may not be generalizable to the full population of interest. In light of this potential result, individualized follow-up care may be a viable solution, by tailoring the number of follow-up visits based on patient preferences and (clinical) characteristics. On the other hand, if participants of the trial seem representative of the target population and a reduced follow-up schedule results in a similar patient satisfaction at lower costs, the current guideline will be adapted and the reduced schedule will be implemented throughout the Netherlands. Furthermore, a reduced follow-up schedule may be applicable to other cancer types and practices outside of the Netherlands.

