Other trials in this field that have been published, including the ENDCAT trial, focus on transitions to (nurse-led) telephone follow-up [12, 13]. Ongoing trials include OPAL, TOPCAT-G, and TOTEM [4]. Similar to ENSURE, OPAL (trial number NCT01853865) is comparing a reduced patient-initiated follow-up compared to standard care and restricted recruitment to low- and intermediate-risk endometrial cancer. TOPCAT-G (trial number ISRCTN45565436) assesses a reduced regime of nurse-led telephone follow-up and includes non-endometrial gynecological cancers but excludes sarcomas and trophoblastic tumors. Unlike others, TOTEM (trial number NCT00916708) has an active arm for more intense follow-up and is uniquely powered to compare survival among endometrial cancer patients.

In conclusion, the ENSURE trial will provide new insights into the (cost-)effectiveness of a reduced follow-up schedule in low-risk endometrial cancer patients and will guide future recommendations for evidence-based follow-up. Results will show whether patients are willing to participate in the trial and thus agree on reduced follow-up. In addition, the non-participation study will provide insight why some patients do not agree to be randomized in one of both study arms. If reduced follow-up results in similar levels of satisfaction and outcomes at lower costs, a reduced schedule can become part of regular follow-up care for early-stage endometrial cancer patients.

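### The 0.5 SD non-inferiority margin is set for all secondary outcomes, including recurrence and survival, where it has no defined scale and tolerates about a doubling or more on each reading tried

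*Protocol article*

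**What the plan says.** Under Statistical analysis, after describing the one-sided primary analysis, the article says: "Secondary outcomes will also be analyzed as non-inferiority using 0.5 SD as a non-inferiority margin, but will be tested two-sided". It excepts no outcome. The same section names linear regression for continuous outcomes and logistic regression for dichotomous ones. It attributes the 0.5 SD figure to a rule of thumb for when a change in a health-status score is meaningful.

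Objectives and hypotheses closes its list of secondary outcomes with "healthcare providers’ satisfaction with follow-up schedule, time till recurrence, and survival". The Abstract's list ends with "fear of recurrence, anxiety and depression, information provision, recurrence, and survival". Neither list separates the clinical events from the questionnaire scales, and no risk-difference or hazard-ratio margin appears anywhere.

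Two event rates are given. The Background puts recurrence in early-stage disease at 3%, without a time horizon. Sample size allows for "patient who die (16%) over five-year follow-up".

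The closing paragraph of the Discussion makes the case for routine use conditional: "If reduced follow-up results in similar levels of satisfaction and outcomes at lower costs". The Abstract likewise anticipates similar overall outcomes in the two arms.

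**The concern.** A margin of half a standard deviation is a convention for scale scores, where the SD measures spread between patients. For a yes/no event the SD is fixed by the event rate. When the event is rare, half of it is large compared with the rate itself. For time to recurrence or death there is no SD to halve without further definition. The rule as written therefore covers two outcomes that it does not fit.

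These outcomes bear on the safety of the arm with fewer visits. A formal label of non-inferior on recurrence or survival could be read as part of the similar outcomes on which the Discussion's closing argument relies. The label would follow mainly from the width of the margin and the scale chosen, not from evidence that the trial can supply.

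**Working it through.** **Inputs.** Margin 0.5 SD (Statistical analysis); recurrence 3% (Background); deaths 16% over five years, 20% loss, 282 patients, 90 per arm in the analysis (Sample size); 1:1 allocation (Design). Hence 282/2 = 141 per arm randomised, and 141 × 0.80 ≈ 113 after 20% loss.

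**The plan's own sample size.** With margin 6, SD 14.3, 80% power and a 1.96 critical value, n = 2 × (14.3/6)² × (1.96 + 0.842)² ≈ 89.2, so 90 per arm and 180 in total. Then 180/(1 − 0.20 − 0.16) = 281.25, so 282. The figures reproduce. They rest on satisfaction alone; recurrence and survival played no part.

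**Reading A: risk difference, SD = √(p(1−p)) (assumed).**
- Recurrence: 0.5 × √(0.03 × 0.97) = 0.0853. Limit 3% + 8.5 points = 11.5%, or 3.8 times the control rate.
- Deaths: 0.5 × √(0.16 × 0.84) = 0.1833. Limit 16% + 18.3 points = 34.3%, or 2.1 times the control rate.

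**Reading B: logistic scale (assumed).** The standard logistic distribution has SD π/√3, so the margin is an odds ratio of exp(0.5 × π/√3) = 2.48. The limits are 7.1% (from 3%) and 32.1% (from 16%), or 2.4 and 2.0 times the control rates.

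**Chance of declaring non-inferiority.** Exact binomial enumeration. Reading A uses the upper limit of a two-sided 95% Newcombe interval, with the margin either fixed at the planning rate or taken from the pooled observed SD. Reading B uses a two-sided 95% Wald interval for the log odds ratio with 0.5 added to each cell. Each cell gives the results for 141 and then 90 per arm.

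| True rates, control v reduced | A, fixed margin | A, observed-SD margin | B, odds ratio 2.48 |
|---|---|---|---|
| Recurrence 3% v 3% | 95%, 80% | 95%, 76% | 26%, 14% |
| Recurrence 3% v 6% | 52%, 34% | 75%, 51% | 5%, 5% |
| Deaths 16% v 24% | 59%, 43% | 72%, 52% | 28%, 20% |

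At 113 per arm, a doubling of recurrence passes 42% (fixed) or 61% (observed SD) of the time on reading A.

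**Observed results that pass on reading A, 141 per arm.** Eight recurrences against 4 give an upper limit of 8.2 points, inside the fixed 8.5. Eleven against 4 give 10.9 points, inside the observed-SD margin of 0.5 × √(0.0532 × 0.9468) = 11.2 points, where 0.0532 = 15/282. Taken from the trial's data, the margin widens as recurrences accumulate.

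**What the trial can estimate.** About 282 × 0.03 ≈ 8 to 9 recurrences are expected. With equal 3% rates the 95% interval for the difference is about ±1.96 × √(2 × 0.03 × 0.97/141) = ±4.0 points, which already includes more than a doubling.

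**The case against.** The best defence is that the margin was meant for the scales only. Its stated source concerns health-status scores. The hypotheses of no worsening in Objectives and hypotheses cover satisfaction, quality of life, fear of recurrence, anxiety, depression and information, but not recurrence or survival. One of the two outcomes is worded as a time to event, for which 0.5 SD has no ready meaning. A full protocol or analysis plan may also treat these outcomes separately. All of this is plausible, but the published sentence covers secondary outcomes without exception. If the authors meant the scales only, a short clause would say so.

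A reader might infer that recurrence of 11.5% or deaths of 34% would be declared non-inferior, or that a pass is almost automatic. The documents do not support either. Those figures are margin limits: with the fixed margin on reading A and 141 per arm, true rates at the limits pass only about 2.5% of the time. On reading B, which matches the regression that the article names for dichotomous outcomes, non-inferiority on recurrence would usually not be declared even with equal arms. The false-reassurance risk is thus specific to the risk-difference reading.

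A reader might also infer that the adoption decision turns on this verdict. The Discussion's statement on changing the guideline is tied to representative participants and "a reduced follow-up schedule results in a similar patient satisfaction at lower costs, the current guideline will be adapted". The closing paragraph refers only to outcomes in general. The Discussion also describes another ongoing trial as the one sized to compare survival, so the authors do not present this trial as powered for that question. The link to adoption is indirect, and the documents give no ground for requiring a rewritten adoption condition.

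**Conclusion.** The point holds as a should-fix. The article sets one margin for all secondary outcomes, and its own lists place recurrence and survival among them. For these two the margin has no stated scale, and both readings tried here tolerate about a doubling or more.

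Depending on the reading, with 90 to 141 per arm, a true doubling of recurrence would be called non-inferior about 34–75% or about 5% of the time. Deaths of 24% against 16% would pass about 43–72% or about 20–28% of the time. Equal 3% recurrence rates would pass about 76–95% or only about 14–26% of the time. A verdict that changes this much with an unstated choice tells the reader little, whichever way it falls.

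The figures assume the two readings above, no clustering or covariate adjustment, and the article's 3% and 16% as control rates; the 3% has no stated horizon. The primary satisfaction comparison is unaffected.

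**What to change.** In Statistical analysis, limit the 0.5 SD non-inferiority margin to the patient-reported scales. Add a sentence such as: Recurrence and survival are outside this rule; the between-arm differences at three and five years will be reported with 95% confidence intervals, and no non-inferiority or similarity claim will be made for them. With that in place, the references to similar outcomes in the Abstract and in the closing paragraph of the Discussion should be understood as referring to the patient-reported outcomes. The Discussion's adoption statement need not be rewritten.

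The cost is wording only, with no extra patients, visits or data. The sponsor gives up a non-inferiority statement on recurrence and survival that the trial is not sized to support.

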### Design

A national multicenter (non-inferiority) RCT among 282 endometrial cancer survivors will be conducted. Patients will be randomized 1:1 in the intervention or control group. Since differences in outcomes between groups are expected to be most pronounced within the first three years of follow-up and the largest cost-saving is achieved within three years, we will evaluate this study in a two-step approach, with an evaluation after one, three, and five years. After five years, the follow-up according to the guideline ends. Patients in both arms receive a Survivorship Care Plan, with information on symptoms which would necessitate a consultation.

Doctors and patients cannot be blinded for intervention or control group assignment. A questionnaire will be sent to all patients at baseline (after primary treatment), and 6, 12, 36, and 60 months later. The baseline questionnaire will be assessed before the intervention under study, that is the different follow-up schedules, starts. Healthcare use, recurrences, survival, and costs will be assessed after three and five years. A schedule of the study is presented in Fig. 1. Healthcare professionals will receive a questionnaire at the end of the study. In addition, a non-participation study will be performed registering hospital healthcare use and assessing patient-reported outcomes using a questionnaire. Medical Ethics approval will be obtained before the start of this project.

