### Recruitment

The national Trial Office of the Netherlands Comprehensive Cancer Organization (IKNL) will organize data collection. Patient-reported outcomes will be obtained by questionnaires [32]. Informed consent will be asked by the treating gynecologist during the postoperative visit. The patient is provided information about the study and an informed consent form. Patients have 2–4 weeks to consider the proposal and can ask questions for instance during an extra visit or a telephone call. In the visit 5–7 weeks after diagnosis, the patient signs the written informed consent and provides address information, in case she is willing to participate. The gynecologist fills out the Randomization Form and sends it to the IKNL Trial Office, who performs the randomization. The patient receives the paper questionnaire and a pre-stamped envelope, to be completed at home. The patients send the completed questionnaire to the IKNL Trial Office. At 6, 12, 36, and 36 months the participant will receive a questionnaire plus pre-stamped envelope at their home address. Non-respondents will be sent a reminder letter and questionnaire within six weeks. Only for the baseline questionnaire will this procedure will be faster to assure a proper baseline measure (reminder through the local principal investigator or research nurse after two weeks). If the patient moves to another hospital, a form will be used to obtain patient data from the new hospital. If the patient does not want to participate in the trial, she is still asked to fill out a single questionnaire and consent to assess healthcare use information, allowing the researchers to compare participants and non-participants. If the patient agrees, the gynecologist completes the registration form for non-participants and sends it to the IKNL Trial Office. The gynecologist provides the patients with a set including a short one-time questionnaire, an informed consent form to assess healthcare use data and a pre-stamped envelope. No other data will be collected for this patient. Questionnaires will be scanned and the database will be checked for a sample of ten patients. On the total database, range and consistency checks will be conducted. Clinical research forms (CRF) will be completed directly in a program.

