### Intervention versus usual care

#### Usual care

The control group receives follow-up care according to Dutch guideline [2] . This guideline proposes follow-up visits every 3–4 months during the first and second years, every 4–6 months during the third year, and every 12 months during the fourth and fifth years after the end of treatment irrespective of stage and grade [2], resulting in a total of 10–13 visits in five years.

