The cost-effectiveness analysis will be performed from a healthcare perspective with a time horizon of 36 months and will be expressed as the incremental cost per QALYs (based on the EQ-5D) and the incremental costs per satisfied patient. Based on results up to 36 months, five-year cost-effectiveness results will be estimated. Patient adherence to the reduced follow-up schedule will explicitly be addressed in the cost-effectiveness analysis. A budget impact analysis will be performed according to the ISPOR guidelines [44]. The budget impact analysis addresses the financial stream of consequences related to the implementation of and compliance with the reduced follow-up scheme to assess affordability. The budget impact will depend on both the cost-savings due to reduced follow-up visits, the uptake by specialists, adherence of patients as well as potential cost increases, e.g. at the level of the primary care physician.

Results of the trial will be published in scientific journals and communicated to the patients via patient organizations.

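### The five-year cost-effectiveness result is based on 36-month data, with no commitment to use the five-year data that the trial collects

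*Protocol article*

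**What the plan says.** The Statistical analysis section of the protocol article sets the economic horizon: "The cost-effectiveness analysis will be performed from a healthcare perspective with a time horizon of 36 months". Results are to be expressed per QALY, with the EQ-5D as the source, and per satisfied patient. The five-year result follows in one sentence: "Based on results up to 36 months, five-year cost-effectiveness results will be estimated". A budget impact analysis comes next.

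The Design section describes longer data collection: "Healthcare use, recurrences, survival, and costs will be assessed after three and five years". It also states: "A questionnaire will be sent to all patients at baseline (after primary treatment), and 6, 12, 36, and 60 months later". The abstract gives the same questionnaire times. The Recruitment section prints them differently ("At 6, 12, 36, and 36 months the participant will receive a questionnaire"), which is probably a misprint for 60 months.

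The Design section describes a two-step evaluation with looks at years 1, 3 and 5. It justifies the three-year focus by saying that most of the difference in outcomes and the largest saving are expected by then. The Statistical analysis section repeats the three analysis times for the trial data in general.

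Under Usual care, control patients are still seen "every 12 months during the fourth and fifth years after the end of treatment". Under Intervention, the four visits fall at 3, 12, 24 and 36 months, and none is scheduled after that.

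**The concern.** The policies being compared are five years of guideline visits and four visits ending at year three. A 36-month horizon stops at the moment the intervention arm enters its phase without scheduled visits. Data up to then cannot show directly whether patients turn to the general practitioner, the nurse or unscheduled specialist visits afterwards, or what late events cost. The protocol treats such substitution as a real possibility, both in its hypotheses and in its description of the budget impact.

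The trial follows patients through exactly this period, yet the only stated basis for the five-year economic result is data up to month 36. The Discussion says that favourable results will lead to a change in the national guideline. The five-year figure and the budget impact would inform that decision, so it matters whether they rest on projection or on observation.

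**Working it through.** **Inputs**
- Control schedule (Usual care): every 3 to 4 months in years 1 and 2, every 4 to 6 months in year 3, yearly in years 4 and 5.
- Intervention schedule (Intervention): 4 visits, the last at month 36.
- Stated control total (Usual care): 10 to 13 visits.

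**Step 1. Reproduce the stated total.**
- Years 1 and 2: 24/4 = 6 to 24/3 = 8.
- Year 3: 12/6 = 2 to 12/4 = 3.
- Years 4 and 5: 2.
- Total: 6 + 2 + 2 = 10 to 8 + 3 + 2 = 13. This matches the protocol.

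**Step 2. Scheduled visits avoided, by horizon.**

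| Horizon | Control | Intervention | Avoided |
|---|---|---|---|
| 36 months | 8 to 11 | 4 | 4 to 7 |
| 60 months | 10 to 13 | 4 | 6 to 9 |

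**Step 3. Share inside and outside the 36-month horizon.**
- Inside: 4/6 = 67% to 7/9 = 78%.
- Outside: 2/6 = 33% to 2/9 = 22%.

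This agrees with the protocol's statement that the largest saving comes within three years. It also shows that a quarter to a third, roughly, comes later.

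**Step 4. Late recurrences.** The Background gives a recurrence rate of 3% and says that 70 to 100% of recurrences occur within three years. In 282 patients that is 282 × 0.03 = 8.5 recurrences, of which 0 to 30%, or 0 to 2.5, would come later. The time base of the 3% is not given, so this is only an order of magnitude. Late recurrences would be few; care sought after visits stop is the larger unknown, and the protocol gives no figure for it.

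**Step 5. What will be available at five years.** The Sample size section expects 20% loss to follow-up and 16% deaths. Adding the two, as the protocol's 282 implies (180/0.64 = 281.25, rounded up to 282), leaves 282 × 0.64 = about 180 patients alive and in follow-up. Deaths are themselves outcomes in a QALY analysis. The missing part is the 20% lost, 282 × 0.20 = about 56 patients. The five-year data would be incomplete but substantial.

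**Step 6. Is the EQ-5D among them?** It is named as the instrument for QALYs, and a questionnaire is sent at 60 months. The content of each questionnaire by time point is not stated in the available text, and the schedule figure is not shown. EQ-5D at 60 months is therefore likely but inferred. Costs, care use, recurrences and survival at five years are stated outright.

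**The case against.** The strongest reply is that the sentence describes a projection made at the three-year evaluation. The Design section has a staged evaluation, and the Statistical analysis section has data analysed again at year 5. On that reading no complete five-year data exist when the estimate is made. This is plausible and stands as a possible intention. But the economic paragraph gives a single horizon, calls nothing interim and plans no update, and a general line about analysis times does not change a horizon set specifically for this outcome.

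A reader might go further and infer that the protocol replaces observed five-year data with a model. The documents do not support that. They name no model, do not say that the five-year data will be set aside, and nowhere exclude a later economic analysis.

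Other points on that side:
- *The horizon is reasoned.* This stands, and the 67 to 78% supports it. The 36-month analysis should be kept.
- *The visit share does not measure harm.* This stands. The two control visits in years 4 and 5 are fixed by the guideline and easy to project. No change in costs, QALYs or the economic conclusion has been shown.
- *Some information on visit-free periods exists by month 36, since intervention visits are a year apart from month 12.* This stands in part. A patient with a visit still ahead may seek care differently from one with none.
- *Five-year data will need imputation and interpolation.* This stands, because no questionnaire falls between months 36 and 60. It calls for careful handling but is no reason to leave the data unused.
- *A journal article condenses the full plan.* An extrapolation method may well be left to the full plan. The horizon and the data source for the five-year result are stated here, however, and those are what the point concerns.

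**Conclusion.** The concern holds in this form: the protocol bases its five-year cost-effectiveness result on data up to 36 months and does not commit to using the five-year costs, care use, recurrences and survival that it collects, or the 60-month questionnaire. The gap matters because the intervention arm's period without scheduled visits begins at month 36 and so lies outside the stated data.

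In size, 2 of the 6 to 9 avoided scheduled visits (22 to 33%) fall after the horizon. This assumes full adherence to both schedules and counts visits only; the effect on costs and QALYs cannot be derived from the document. Use of 60-month QALYs assumes that the EQ-5D is in that questionnaire. If the sponsor already intends the sentence as a three-year projection to be updated later, only the wording needs to change.

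**What to change.** In the Statistical analysis section:
1. Keep the 36-month analysis and label the five-year estimate derived from it as an interim projection.
2. State that at the five-year evaluation cost-effectiveness is re-estimated from the observed 60-month costs, care use, recurrences and deaths, and from the EQ-5D if it is in the 60-month questionnaire. State how missing data are handled.
3. State that this result supersedes the projection and updates the budget impact analysis.
4. Confirm whether the 60-month questionnaire includes the EQ-5D, and correct the questionnaire times printed under Recruitment.

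The cost is one further run of the economic analysis on data already planned, with some interpolation and imputation between months 36 and 60. The definitive five-year result comes two years after the projection, while the three-year result is still reported on time.
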